**The Case for Pre-operative Very Low Calorie Diets (VLCDs) in Obese Endometrial Cancer Patients.**

Version 3

13.08.2017

SYNOPSIS

Protocol title: The Case for Pre-operative Very Low Calorie Diets (VLCDs) in Obese Endometrial Cancer Patients.

Short title: Pre-operative Optifast in Obese Endometrial Cancer Patients.

Protocol version: 3

LIST OF INVESTIGATORS

Principal Investigator: [name]

Organisation: King Edward Memorial Hospital

Address: [name]

[contact]

Email: [contact]

Principal Investigator: [name]

Organisation: St John Of God Subiaco Hospital

Address: [name]

[contact]

Email: [contact]

Associate Investigator: [name] [name]

Organisation: St John Of God Subiaco Hospital

Address: [name]

[contact]

Email: [contact]

Associate Investigator: [name]

Organisation: King Edward Memorial Hospital

Address: [name]

[contact]

Email: [contact]

SUMMARY

Study title: The Case for Pre-operative Very Low Calorie Diets (VLCDs) in Obese Endometrial Cancer Patients.

Short title: Pre-operative Optifast in Obese Endometrial Cancer Patients.

Protocol version: 1

Objectives

Primary objective:

-To evaluate the feasibility of a 4-6 week pre-operative very low calorie diet (VLCD) with Optifast® in severely obese (BMI ≥ 35) low risk endometrial cancer patients (Grade 1 endometrioid adenocarcinoma with no or minimal myometrial invasion) planned to undergo a laparoscopic hysterectomy. Dietary compliance will be assessed by urinary ketone reagent strips.

Secondary objectives:

-To monitor changes over the 4-6 week VLCD period in body weight, BMI, anthropometric measures (hip and waist circumference), clinical variables of blood pressure and biochemical variables (fasting blood sugar and cholesterol).

-To evaluate tolerability of the VLCD using a validated qualitative questionnaire.

-To collect data on surgical outcomes.

Study design: This is a single institution (St John of God Subiaco Hospital) prospective observational study of women in Western Australia diagnosed with low risk endometrial cancer, BMI ≥35, planned to undergo a laparoscopic hysterectomy.

Planned sample size and selection criteria: The study will aim to recruit 20 patients over a 12 month period and will include women recommended to have Optifast as part of their pre-operative preparation for surgery.

Study procedure: Women aged 18-65 years with a low risk endometrial cancer of the uterus with a BMI ≥35 who have been recommended to have a very low calorie diet prior to planned surgery will be invited by their Gynaecological Oncologist to participate in this observational study. They will be given the relevant information package and consent forms to read at their initial consultation. If they agree to consent to the study, they will have an initial nutrition assessment with a dietitian. This will include performing baseline fasting blood tests, anthropometric and blood pressure measurements, in addition to the provision of written and verbal information regarding following a VLCD pre-operatively. Patients will then be required to have fortnightly contact with the dietitian, either face-to-face or over the phone, for 4-6 weeks to facilitate dietary adherence and success. Urinary ketones will be measured fortnightly to assess dietary compliance. The 4-6 week time frame will be at the discretion of the treating Gynaecological Oncologist. Clinical data will be recorded and the data collected will be de-identified. On the day of surgery additional fasting blood tests will be collected in the operating theatre. Australian Clinical Labs will be responsible for processing all blood samples. Biospecimens obtained at surgery will undergo routine cytology and histopathology by the Anatomical Pathology Department at Australian Clinical Labs. Operative data will be recorded. Tumour stage, grade and ongoing management plan will be ascertained from the minutes of the weekly combined King Edward Memorial Hospital and St John of God Subiaco Hospital tumour conference. Additional information on post-operative course will be obtained from the patient’s discharge summary.

Statistical considerations: The sample size for this observational, proof of concept study is pragmatic and analysis of will be descriptive. The findings of this study will facilitate calculation of the sample size calculation for a subsequent, appropriately powered, randomized controlled trial. Data analysis will be performed using the statistical software IBM SPSS Statistics Version 20.

Duration of the Study: Time taken to enroll patients and collect clinical data is estimated to take 12-18 months. Complete analysis of all data may take up to 2 years.

1. BACKGROUND

1.1 Study Background

Endometrial cancer is the most common gynaecological malignancy in Australia with 2652 new cases estimated to be diagnosed this year^1^. Over the past 30 years, the incidence and mortality of endometrial cancer has continued to rise^2,3^ coinciding with a national epidemic of obesity. Endometrial cancer ranks highest amongst all cancers in its association with obesity - every 5mg/m^2^ increase in BMI confers a 1.6 fold increased risk of endometrial cancer^4^. According to the Australian Bureau of Statistics, 56% of Australian adult women are now overweight or obese based on body mass index with 28% classified as obese (BMI≥30)^5.^

Fortunately studies have shown an inverse relationship between BMI and tumor biology. Most obese women with endometrial cancer have a tendency towards a slightly more favorable histopathological phenotype with MSI (microsatellite instability) negative, early stage and lower grade tumours^6-8.^

Surgery is the mainstay of endometrial cancer treatment, which includes the removal of the uterus, fallopian tubes, ovaries, with pelvic and para-aortic lymphadenectomy as necessary for surgical staging and management planning. Obesity and its associated fat deposition posess significant challenges to the performance of safe surgery by any technique, whether open or minimally invasive.

Minimally invasive surgery is now recognized as a safe and feasible surgical alternative to laparotomy for morbidly obese women with endometrial cancer ^9,10^. Some studies have shown increased conversion rates^11,12^ and decreased success in obtaining pelvic and para-aortic lymph nodes in obese women^12-14^ however other smaller retrospective studies have shown comparable conversion rates to women of lower BMI^15-17^ and successful pelvic lymphadenectomy^18^. Some studies even show superiority of a laparoscopic approach in regards to surgical complications in the morbidly obese^19-21^.

Despite improvements in anaesthesiology and surgical techniques obesity remains a risk factor for surgery and in some cases delaying surgery until a patient has lost weight to improve peri-operative outcomes and performance status may be advisable.

Non-surgical treatment of low-grade endometrial malignancies with morbid obesity and comorbidities has been directed at restoring the oestrogen-progesterone balance, typically through the addition of progestins. This strategy is often effective but commonly associated with depression and secondary weight gain, which are problematic in the obese. There are no large published case series however reporting on such medical management as primary treatment (feMMe study in progress) and the literature is often focused on younger women who desire fertility preservation^33^ which makes it difficult to apply to the older obese endometrial cancer population. Furthermore these therapies do little to relieve the cardiovascular and endocrine consequences of morbid obesity^37^.

Very Low Calorie Diets (VLCDs), however, can provide safe rapid weight loss in the period immediately preceding surgery and may reduce the perceived perioperative difficulties associated with anaesthetic and surgical techniques. This method of short-term dietary therapy is often overlooked despite being an evidence-based practice supported by the Dietitians Association of Australia (DAA). VLCDs provide 800kcal per day and rank second after bariatric surgery in their ability to help overweight or obese adults lose weight (14.7% mean weight loss at 4-20 weeks) (NHMRC 2006). Patients with a BMI ≥35 can be expected to lose 1.5-2.5kg per week^23^.

VLCDs safely and effectively achieve significant reductions in body weight, liver volume and visceral/subcutaneous adipose tissue. Interestingly 80% of the reduction in liver volume occurs in the first 2 weeks of a VLCD^22^ (see Figure 1). Many of the metabolic and physiologic effects of VLCDs are also beneficial, such as improvement in insulin sensitivity and fasting plasma glucose levels enabling a reduction or even cessation of diabetic medications, lowering of blood pressure and serum triglyceride values ^23,24^. VLCDs are also conducive to ketosis, which can help suppress hunger and preserve lean muscle tissue^23^.

[figure not shown]

Figure 1: Relative changes in liver volume, visceral adipose tissue and body weight during a 12-week very low calorie diet as measured by serial MRI^22^.

Pre-operative VLCDs such as Optifast^®^ have been used successfully to reduce the perceived technical difficulty and perioperative complications in bariatric surgery, general surgery and more recently in laparoscopic cholecystectomy^25-27^. VLCDs prior to bariatric surgery have well-established benefits. In a multicentre randomized trial, Van Niewenhove et al^26^ investigated the impact of a 2 week preoperative VLCD before laparoscopic gastric bypass surgery in 273 patients with a BMI ≥35. 10.7% of the patients in the VLCD group were not able to complete the diet due to intolerance or non-compliance, however, those who adhered to the VLCD lost 4.9kg compared to 0.4kg in the control group (P <0.001). The surgeons’ perceived difficulty of the procedure (using visual analog score) was also lower in the VLCD group as was the number of post-operative complications; in particular infections at the 30-day follow. Pekkarinen^25^ examined the suitability of a 7-24 week VLCD in general surgical patients with a BMI ≥35 whose elective surgery was postponed because of their obesity. Two patients discontinued and the mean weight loss of the remaining 28 patients was 19.6kg (15% of initial weight). Remarkably in four patients, an operation was no longer necessary after weight loss. More recently, the effectiveness of a 2-week preoperative VLCD in 38 laparoscopic cholecystectomy patients has been investigated^27^. Even though only 32% (6/19) of obese patients (BMI >30) adhered to the VLCD, with a mean weight loss of 2.75kg, the technical difficulty of both the liver retraction and dissection of Calot’s triangle was reduced in those obese patients who adhered to the VLCD compared to the non-compliant obese group. This was thought to be the result of the reduction in liver volume caused by caloric restriction. This was in turn postulated to reduce complications such as bile duct injury.

The compliance rate for short term VLCD’s of 2-24 weeks duration is surprisingly high at 86-96%^22,24-25,31^. Previous studies of VLCDs have shown that hunger and emotional eating increased, and taste acceptability decreased significantly between week 4 and week 10, most likely related to boredom and fatigue with the ongoing dietary restriction^22^. Accordingly, a 6-week time frame has been proposed to achieve maximal liver volume reduction and significant reductions in VAT and body weight without compromising compliance and acceptibility^22^.

VLCDs such as Optifast are routinely employed pre-operatively in many Gynaecological Cancer Units across Australia in the low risk obese endometrial cancer population. However, despite their growing popularity, the feasibility, tolerability and efficacy of these diets has not been investigated in this patient group. A 4-6 week time frame seems reasonable to achieve the greatest benefit safely without delaying surgery or compromising patient adherence and tolerability.

**1.2 Rationale for performing the study**

The rationale of the study is to document the feasibility, tolerability and efficacy of a Very Low Calorie Diet (VLCD) with Optifast in obese endometrial cancer patients by assessing compliance and weight loss. A secondary objective is to measure patients’ metabolic profiles prior to, and following, the intervention to provide data to inform further research.

**2 STUDY OBJECTIVES**

**2.1 Primary Outcome**

The number/percentage of patients with urinary ketone reagent testing suggesting dietary compliance with the 4-6 week very low calorie diet (Optifast) will be the primary outcome measure.

**2.2 Secondary Outcomes**

Secondary outcomes will include:

-Monitoring changes over the 4-6 week VLCD period in body weight, BMI, anthropometric measures (hip and waist circumference), blood pressure and serum biochemistry.

-Evaluating patient tolerability of the VLCD using a validated qualitative questionnaire.

-Collecting data on surgical outcomes.

**3 STUDY DESIGN**

**3.1 Design and study group**

This is a prospective observational study investigating obese (BMI ≥ 35) women with low risk (early stage, low grade endometrioid histology) endometrial cancer planned to undergo laparoscopic hysterectomy.

In addition to the routine information obtained from the initial visit history form (see appendices 10.1), the following information will be recorded:

- Geographical location (rural or local)
- Histology at diagnosis
- Any current non-surgical treatment for endometrial cancer (e.g. Mirena or Provera)
- Any previous history of weight loss, pharmacotherapy or enrolment in weight control programs and amount of weight lost and for how long

The pre-operative Very Low Calorie Diet will be with Optifast® and involves a 4-6 week ‘Intensive Phase’, 800 kcal (<3,300kJ) per day containing all RDI of protein, carbohydrate, essential fatty acids, fibre, vitamins, minerals and trace elements. 3 Optifast VLCD products must replace regular main meals (shakes, soups, desserts or bars). A Minimum of 2 cups of low starch vegetables are allowed per day in addition to 1tsp oil per day to help the gallbladder contract in the absence of additional fat in the diet. A minimum of 2L water and other calorie free beverages each day is allowed. Alcohol consumption is discouraged during the VLCD, however, if this is too difficult for patients, then 1-3 standard drinks per week is the maximum allowed.

As part of this particular research project, participants will have their dietary compliance assessed by urine tests, tolerability of the Optifast diet assessed by questionnaires, additional body measurements and blood tests performed.

Urinary ketone reagent strips will be used to assess dietary compliance. After the first week of a VLCD, an increase in the urinary excretion of ketoacids occurs subsequent to increased fat catabolism; therefore the presence of at least trace ketones in the urine is considered to indicate net lipolysis and dietary adherence^22,30^. Urine samples are to be collected fortnightly at the dietitian or local GP consultation. The absence of ketones is scored 0, trace 1, small amount 2, moderate amount 3. Ketone scores determined at visits every 2 weeks will be summed for each patient.

A validated questionnaire of product side effects and acceptability^22^ will be used. Subjects will be asked to rate 6 factors of product taste, hunger, nausea/vomiting, bowel function, emotional eating and social eating on a 5 point Likert scale (see appendices 10.2).

Anthropometric measurements of height (using a wall-mounted stadiometre), weight (wearing light clothing, no shoes), BMI (weight kg/height m^2^), waist circumference (narrowest point between low rib margin and iliac crest) and hip circumference (widest point over greater trochanters) will be recorded at baseline and fortnightly preferably by the same clinician or their appropriate delegate. Seated blood pressure will be measured at baseline and fortnightly. Blood tests will be taken at baseline and again on the day of surgery (after 4-6 weeks of Optifast) including FBC, EUC, LFTs, CMP, uric acid, CA125, iron studies, fasting lipid profile (Total cholesterol, LDL, HDL, TG), fasting glucose metabolism (plasma glucose, plasma insulin, HBA1C) and 25OHVitD.

All patients will be given instructions on pre operative fasting and be allowed clear fluids up to 2 hours and solids up until 6 hours prior to induction of anaesthetic as per ERAS recommendations. Randomized controlled trials on mechanical bowel preparation have shown no improvement in surgical exposure or bowel handling in laparoscopic gynaecologic procedures^34-35^.

For the laparoscopic hysterectomy, all patients will receive 2g Cephazolin and 500mg metronidazole 15-60 minutes prior to skin incision (as per eTG 2006). Clindamycin (or Lincomycin) 600mg can be used for patients who are allergic to penicillin.

Additional information will be recorded post operatively on:

- Tumour stage, grade, histological type, degree of myoinvasion
- Lymphadenectomy performed – Yes or No
  - Pelvic vs. para-aortic nodes
  - Sentinel lymph node biopsy vs. debulking of enlarged nodes vs. full pelvic lymph node dissection
  - Number of nodes removed
  - Number of nodes positive
- Adjuvant treatment recommendation from multidisciplinary meeting/tumour board
- ASA and Anaesthetic time
- Operating time
- Surgical complications – urinary tract, vascular or bowel injury; cardiac/pulmonary complications; wound breakdown; infection; estimated blood loss
- Length of hospital stay

Post operatively all patients will returns to a normal diet. There will be no planned refeeding period. They will be offered a follow up with dietitian 1 month post operatively and either adopt the Optifast® program with progression to ‘Maintenance Phase’ or a healthy lower calorie diet. Referral to community/private dietitian will be provided beyond 1 year.

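### Compliance is scored from the ketone concentration in a single urine sample with no dilution control, on a diet with a 2 L daily fluid minimum, so an adherent woman with dilute urine can score 0

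*Protocol*

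**What the plan says.** Protocol section 2.1 defines the primary outcome as "The number/percentage of patients with urinary ketone reagent testing suggesting dietary compliance" with the diet.

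Section 3.1 gives the measurement:

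- **Rationale:** "After the first week of a VLCD, an increase in the urinary excretion of ketoacids occurs subsequent to increased fat catabolism".
- **Criterion for a sample:** "the presence of at least trace ketones in the urine is considered to indicate net lipolysis and dietary adherence".
- **Grading:** "The absence of ketones is scored 0, trace 1, small amount 2, moderate amount 3". The scores from the fortnightly visits are then added up for each woman.
- **Sampling:** "Urine samples are to be collected fortnightly at the dietitian or local GP consultation". Sections 5.1 and 5.2 add a sample on the day of surgery, so a woman on the 4-week programme gives 2 samples and a woman on the 6-week programme gives 3.
- **Fluids on the diet:** "A minimum of 2L water and other calorie free beverages each day is allowed". No upper limit is given.

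Section 3.2 aims for twenty women. Section 7.1 calls the sample size pragmatic and the analysis descriptive, and says the findings will support the sample size of a later randomised trial.

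**The concern.** The rationale and the instrument measure different things. More ketoacid excreted means a larger amount leaving the body over time. A reagent strip reports concentration in one void. The two agree only if urine volume is roughly constant, and the protocol neither holds volume constant nor measures it. The diet it describes includes a generous fluid minimum.

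The error has a direction. For a given excretion, more dilute urine pushes the reading down a grade or to 0. A woman who keeps to the diet and drinks as described could be scored as though she had not complied. The summed score falls whenever a grade is lost. The primary percentage falls if the loss takes her below whatever patient-level rule is applied. An understated compliance figure would also carry into the planning of the later trial.

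This cannot be left to the analysis stage. If specific gravity and collection time are not recorded when the sample is taken, they cannot be recovered.

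**Working it through.** The protocol gives no strip error rate, detection limit or expected ketone level, so there is no stated figure to reproduce. The check has four steps.

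**1. Is there a dilution control anywhere?** The protocol's text on urine testing (sections 2.1, 3.1, 5.1 and 5.2) mentions no specific gravity, urinary creatinine, first-void or timed collection, record of recent fluid intake, or repeat of a negative. The blood panel in 3.1 has no ketone measurement. Nothing in the plan can override a strip negative for the primary outcome.

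**2. What does dilution do to the reading?** At fixed excretion *E* and urine volume *V*, concentration is *C = E/V*. Relative to a reference volume:

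- 1.5 times the volume: 1/1.5 = 0.67
- 2 times: 1/2 = 0.50
- 3 times: 1/3 = 0.33

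These ratios are illustrative. The protocol gives a fluid intake, not a urine output, and no pre-diet comparison. A fall matters for the absent/trace boundary only if it crosses the strip's trace limit.

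**3. What is one woman worth?** 1/20 = 5 percentage points.

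**4. When does a misread sample misclassify a woman?** Section 3.1 fixes a criterion for a sample and a sum for a woman, but no cut-off that makes a woman compliant. Assume, for illustration only, that a sample from an adherent woman reads 0 with probability *f*, independently across her *k* samples. If every woman is truly adherent, observed compliance is:

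- all samples must be positive: (1 − *f*)^*k*
- one positive sample is enough: 1 − *f*^*k*

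| Assumed *f* | All positive, *k* = 2 | All positive, *k* = 3 | Any positive, *k* = 2 | Any positive, *k* = 3 |
| --- | --- | --- | --- | --- |
| 5% | 90% | 86% | 99.8% | 100.0% |
| 10% | 81% | 73% | 99% | 99.9% |
| 20% | 64% | 51% | 96% | 99% |

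Section 1.1 cites compliance of 86–96% in earlier studies. Taking that as the true rate with *f* = 10%:

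- all-positive rule, 2 samples: 0.86 × 0.81 = 70% to 0.96 × 0.81 = 78%
- all-positive rule, 3 samples: 0.86 × 0.729 = 63% to 0.96 × 0.729 = 70%
- any-positive rule: 85–95% (2 samples) or about 86–96% (3 samples)

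Independence is a simplification. A woman who habitually drinks a lot would tend to have dilute urine at every visit, which makes the any-positive rule less protective and the all-positive rule less damaging than shown.

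**The case against.** Trace is the lowest positive grade, so the threshold is already as lenient as the strip allows. The sentence on fluids says the amount is allowed, so reading it as an instruction is fair but not certain. Nothing shows that women who follow the diet best also drink most. Fortnightly weight (3.1) and the questionnaire items on eating outside the diet (10.2) would help to interpret a surprising negative. The study is small, descriptive and a proof of concept. All of this stands and limits the point. It does not remove it: a lenient threshold reduces false negatives without abolishing them, and neither weight nor the questionnaire enters the primary outcome.

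Three stronger readings are tempting, and the documents do not support them.

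- **That the absent/trace cut on a sample decides the primary outcome.** It decides a sample. The step from sample to woman is unstated, and the table shows that this step governs most of the damage.
- **That the primary percentage is understated by a definite amount, say 10 to 20 points.** That would need 2 to 4 of the 20 women to be misclassified (2/20 to 4/20), and nothing in the protocol yields such a count.
- **That scores will rise artificially on the day of surgery because women are less hydrated.** The fasting rule is that women will "be allowed clear fluids up to 2 hours and solids up until 6 hours prior to induction of anaesthetic". That is a short fluid restriction, and the urine sample is not timed against it. Loss of solids could raise ketones by itself, which is a separate matter from dilution.

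**Conclusion.** The point holds as a weakness in the validity of the only primary measure. The protocol argues from an amount excreted, scores a concentration in a single sample, sets a fluid minimum in the same section and controls for dilution nowhere. A dilute sample from an adherent woman can score 0, lowering her summed score and possibly the primary percentage.

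The size is unknown from the documents. What can be said is that each misclassified woman costs 5 points at *n* = 20. The effect lies between negligible and large according to two things the protocol does not give: the false-negative rate per sample and the rule that turns 2 or 3 readings into a compliant woman. The percentages above rest on assumed values of *f* and on independence between samples. They show sensitivity and are not estimates. This is an inexpensive improvement worth making before sampling begins, and no reason to doubt the design as a whole.

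**What to change.** In section 3.1:

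1. Record specific gravity on the same urine sample, using a multi-pad strip.
2. Collect on-diet samples at a standard time of day or, where local consultations make that impractical, record the time.
3. Prespecify a specific-gravity cut below which a negative ketone reading is classed as indeterminate. The documents give no value, so the investigators must choose one and justify it.
4. State the patient-level rule, then report the primary percentage twice: with indeterminates counted as non-compliant, and with them excluded. The first leans low and the second leans high, so together they show how much dilution could matter.
5. Give the mean score per determinate sample beside the sum. Removing a 0 leaves a sum unchanged: scores of 0 and 2 total 2 either way, while the mean goes from 1 to 2.

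Do not repeat only the dilute negatives. That gives some women a second chance to test positive while every positive stands, and it would push compliance upward.

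The cost is protocol wording, one extra field for specific gravity, a note of the time where it is not fixed, and a few readings that become indeterminate. No extra visit or sample is needed, and the diet's fluid instruction does not change.

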**5.2 Scheduled Visits**

| Interventions | Enrolment Visit at initial consultation | Start VLCD | 2 weeks of VLCD | 4 weeks VLCD (if on 6 week program only) | On day of Surgery (both 4 and 6 week patients) |
| --- | --- | --- | --- | --- | --- |
| Informed Consent | ✓ |  |  |  |  |
| Inclusion/exclusion criteria, recording of history, physical exam | ✓ |  |  |  |  |
| Dietitian/ Anthropometric measures, BP |  | ✓ | ✓ | ✓ | ✓ |
| Fasting blood tests |  | ✓ |  |  | ✓ |
| Urine ketones |  |  | ✓ | ✓ | ✓ |
| Patient questionnaire re: VLCD |  |  | ✓ | ✓ | ✓ |
| Tissue collected for analysis |  |  |  |  | ✓ |

Not all of the above interventions are part of routine care for a patient diagnosed with an endometrial cancer. Whilst height, weight, BMI and BP are routine measurements at the initial consultation, anthropometric measures such as waist and hip circumference are not. All anthropometric measurements will be performed at baseline and fortnightly (on 2-3 occasions). Having a blood test (FBC, EUC, LFTs, CMP, coagulation profile, CA125) at baseline and on the day of surgery is routine (G&H) hence the additional tests particular to this research (uric acid, iron studies, fasting lipid profile -Total cholesterol, LDL, HDL, TG - fasting glucose metabolism -plasma glucose, plasma insulin, HBA1C -and 25OHVitD) required for the study can be performed at the time as the routine tests to avoid further invasive procedures. The patient will be required to provide a urine sample for urine ketone testing on 2-3 occasions. They will also be required to complete a 6 point likert questionnaire on 2-3 occasions. There will be fortnightly contact with the dietitian or local GP, either face-to-face or over the phone to facilitate dietary adherence and success.

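### The only per-woman ketone aggregate in the protocol is a raw sum over two tests (4-week programme) or three (6-week programme), so it is not comparable between women and is a poor basis for the primary compliance percentage

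*Protocol*

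**What the plan says.** Protocol 2.1 makes the primary outcome a count of women: "The number/percentage of patients with urinary ketone reagent testing suggesting dietary compliance with the 4-6 week very low calorie diet (Optifast").

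Protocol 3.1 supplies two elements for judging compliance from the strips. The first is a criterion for a single test: "the presence of at least trace ketones in the urine is considered to indicate net lipolysis and dietary adherence". The second is a graded score, "The absence of ketones is scored 0, trace 1, small amount 2, moderate amount 3", with an instruction for combining tests within a woman: "Ketone scores determined at visits every 2 weeks will be summed for each patient".

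The number of tests is not the same for everyone. Protocol 5.2 says: "The patient will be required to provide a urine sample for urine ketone testing on 2-3 occasions". The flow chart (5.1) and the visit table (5.2) show why: the week-4 visit exists only for women on the 6-week programme, while week 2 and the day of surgery apply to all. The Summary says who chooses the length: "The 4-6 week time frame will be at the discretion of the treating Gynaecological Oncologist".

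Section 7.1 plans a descriptive analysis only. The protocol gives no cut-off for the sum and no adjustment for the number of tests, and it does not say how many tests must meet the threshold for a woman to count as compliant.

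**The concern.** The primary result needs a yes or no for each woman. The only instruction that combines her tests is a sum, and a sum over two tests is on a different scale from a sum over three. Two women with the same ketone result at every visit receive different totals because their surgeons booked different dates. The sum also rewards one strong reading as much as several weak ones, although the adherence criterion in the same paragraph asks only whether ketones are present.

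Compliance is the feasibility answer, and section 7.1 says the findings will feed the sample size of a later randomised trial. With 20 women, each woman reclassified moves the percentage by 1/20 = 5 points.

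**Working it through.** **Inputs.** Score per test 0, 1, 2 or 3 (3.1). Adherence threshold per test: score of 1 or more (3.1). Visits with urine ketones: 5.1 and 5.2. Sample size 20 (3.2).

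**1. Reproduce the number of tests.** 4-week programme: week 2 + day of surgery = 2. 6-week programme: week 2 + week 4 + day of surgery = 3. This agrees with the 2-3 occasions stated in 5.2.

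**2. Scale of the sum.** With k tests the maximum is 3 × k, so 6 for k = 2 and 9 for k = 3. A woman with the same score s at every test totals s × k:

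| Result at every test | 2 tests | 3 tests |
| --- | --- | --- |
| none (0) | 0 | 0 |
| trace (1) | 2 | 3 |
| small (2) | 4 | 6 |
| moderate (3) | 6 | 9 |

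The ratio is 3/2 = 1.5 wherever any ketones are present.

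**3. Sum against the protocol's own threshold.** All 4^k score patterns were listed (16 for two tests, 64 for three) and split by whether every test met the threshold:

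| | 2 tests | 3 tests |
| --- | --- | --- |
| Sums when every test is positive | 2 to 6 | 3 to 9 |
| Sums when at least one test is negative | 0 to 3 | 0 to 6 |
| Ambiguous sums | 2-3 | 3-6 |
| Certainly at least one negative | 1 or less | 2 or less |
| Certainly all positive | 4 or more | 7 or more |

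For example, a total of 3 can be 1+1+1 or 3+0+0 on 6 weeks, or 0+3 on 4 weeks. These are possible patterns, not expected frequencies of patients.

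**4. One cut-off applied to all women.** As an illustration, assume that all 20 women show trace ketones at every test, so that every test meets the threshold. Totals are 2 (4-week) and 3 (6-week).
- Cut-off 3: only 6-week women pass. With 5, 10 or 15 women on 6 weeks, compliance is 5/20 = 25%, 10/20 = 50% or 15/20 = 75%.
- Cut-off 2: all pass, but so would a 6-week woman with 2+0+0.
- Cut-off 1 (any test positive): assuming independent tests, each positive with probability 0.80, the chance is 1 − 0.2² = 96% with two tests and 1 − 0.2³ = 99.2% with three.
- Cut-offs 7 to 9: out of reach on 4 weeks.

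**5. How much information the sum keeps.** Assume probabilities for scores 0/1/2/3 of 0.1/0.3/0.3/0.3 in adherent women and 0.7/0.2/0.07/0.03 in non-adherent women. The sum pooled over programmes then separates the two groups with an AUC of 0.93 to 0.95 when 25% to 75% of women are on 6 weeks. Among equally adherent women, a 6-week woman outscores a 4-week woman with probability 0.79 (ties counted half).

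**6. Check of the alternative.** The mean score per test runs from 0 to 3 in both programmes, and trace at every test gives 1.0 in both. The expected share of positive tests is also the same in both. A cut-off on that share is not free of length, however. Take p as an assumed, independent per-test positive rate:

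| Rule: all tests positive | p = 0.80 | p = 0.90 | p = 0.96 |
| --- | --- | --- | --- |
| 2 tests, p² | 64% | 81% | 92% |
| 3 tests, p³ | 51% | 73% | 88% |

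A cut-off between one half and two thirds works the other way. At p = 0.90, at least two of three gives 3 × 0.9² × 0.1 + 0.9³ = 0.243 + 0.729 = 97%, against 81% for both of two.

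**The case against.** The best defence is that the primary percentage may never touch the sum. The per-test threshold stands in the same paragraph, the outcome wording in 2.1 fits it, and no section says that the percentage is derived from the total. The sum could be a descriptive intensity score, and a patient-level rule could sit in a statistical analysis plan that is not at hand. The study is also small, single-group and descriptive, with no planned comparison of 4-week and 6-week women. Scores are taken visit by visit, so a per-test rule can still be computed.

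Much of this stands, and it rules out several stronger readings that a reader might infer:
- That the sum is the sole scoring rule for the primary outcome. It is the sole rule for combining a woman's tests; the threshold is also there.
- That the sum contradicts the threshold. A threshold per test and a graded total can coexist.
- That the sum merely measures programme length, or cannot tell compliant from non-compliant women. A woman with no ketones scores 0 on either programme, the low and high ends are unambiguous, and under the assumptions in step 5 the sum keeps much information.
- That a missed test counts as 0. The protocol does not say how missed tests are scored.
- That the reported percentage will be wrong. That depends on a cut-off that the protocol does not state.

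The defence does not remove the point. The unadjusted sum is written into the protocol, not left open. A later plan that put one cut-off on it would inherit the problem. As a descriptive score alone, it would still not be comparable between the two programmes.

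**Conclusion.** The point holds in a limited form. The stated aggregate is not comparable between women: its maximum is 6 or 9, and identical results at every test differ by a factor of 1.5 purely through programme length. Within a programme it is ambiguous at 2-3 (two tests) and 3-6 (three tests) as to whether every test met the protocol's threshold. If the primary percentage were obtained from one cut-off on the sum, it would depend on the 4-week/6-week mix. In the deliberately extreme illustration it ran from 25% to 75% with no difference in ketone results.

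The scale and overlap results follow from the protocol alone. The illustrations rest on assumed score probabilities, independent tests and assumed programme mixes. They show direction and possible size, and they do not predict the study's result.

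**What to change.** In 3.1 and 2.1, replace the sum as the measure of compliance:
- Base each woman's compliance on the protocol's own per-test threshold, as the share of her scheduled tests with at least trace ketones, and fix the cut-off on that share before data are seen.
- Count tests missed because the diet was stopped as not compliant.
- Report n/N overall and by programme length.
- If intensity is of interest, report the mean score per test (0-3), not the sum.

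Judging all women on weeks 2 and 4 only would equalise the number of tests, but it is less suitable. It leaves week 6 out of an outcome defined on the 4-6 week diet, and it pairs a day-of-surgery test in 4-week women with a mid-diet test in 6-week women.

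The cost is a short text change and no new data. Reported compliance may be slightly lower. A cut-off requiring every test to be positive is somewhat harder to meet with three tests than with two (73% v 81% at an assumed 0.90 per test), and other cut-offs can lean the other way. The results by programme length should therefore always accompany the overall figure.
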